### 3.9. Data Protection

All outcome data will be recorded on different electronic spreadsheets by two researchers, and the accuracy of the data will be checked by the research coordinators. Participant data will be kept in a password-protected personal computer and stored in a properly selected closed room. The privacy of the participants and their personal medical records will be guaranteed by treating the data according to the latest European Union General Data Protection Regulation (2016/679).

### 3.10. Statistical Analysis

In the first qualitative phase, descriptive statistics, chi-squared tests and mixed models of analysis will be employed. Regression analyses will be conducted to determine if different variables (e.g., distance from dialysis center and presence of a caregiver) might interfere with patients’ decisions. Furthermore, the physical activity level and physiological and psychological variables assessed at baseline will be considered independent variables in the regression models.

In the second phase, standard methods of analysis for clinical trials will be used. First, baseline comparisons of patient characteristics for each group will be compared for demographics and primary and secondary outcome measures. The data distribution will also be verified through a Shapiro–Wilk test. A two-way repeated measure analysis of variance will be used to compare differences in the primary and secondary outcomes. Within-group comparisons will be performed via paired Student’s t-tests or Wilcoxon tests, as appropriate. If a significantly different distribution between the baseline characteristics of the group is identified, a secondary analysis that employs multivariate modeling to adjust for these factors will be performed (e.g., linear mixed models for repeated-measures analyses with unbalanced design). Moreover, Kaplan–Meier analysis and Cox regression will be used to model incidence rates for long-term clinical outcomes (hospitalization rate and death). Finally, a post hoc power analysis will also be carried out to determine the clinical impact of the findings.

All analyses will be conducted using intention-to-treat. Missing values, though we will make any effort possible to reduce their incidence, will be treated using the multiple imputation procedure. Moreover, a per-protocol analysis to assess the stability of the study’s conclusions will also be performed. Properly gender-oriented analyses will be carried out for most of the outcomes. A *p* value of 0.05 will be considered statistically significant.

Statistical analysis will be performed with SPSS 21.0 (IBM, Armonk, NY, USA) and MedCalc statistical software (version 19.4.0 and following, MedCalc Software bvba, Ostend, Belgium).

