To fulfill these requirements in the ESKD population, several physical, psychological and environmental barriers that are still present need to be overcome. First, the identification of sustainable programs with good adherence is a priority because of these barriers [18,19,20]. Moreover, a proactive dialysis staff attitude is another crucial issue [21,22]; unfortunately, physical activity and exercise management are not routinely addressed in the care of these patients [2]. Although motivators to exercise have been reported in other diseases [23], nurse-led disease management programs in patients on dialysis have been tested [24,25] but not for promoting physical activity.

This pragmatic trial aims to test the impact of the regular presence of an exercise facilitator in a dialysis center to promote physical activity in the ESKD population. The efficacy will be verified in terms of applicability and feasibility, and the preferred and most effective exercise pathways for the patients will be identified. Secondarily, the study aims to carry out exploratory analyses to evaluate the impact of different exercise interventions on the functional and clinical parameters of the patients.

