## 3. Procedures

### 3.1. Phase 1

In this phase, the exercise facilitator (EF) will be set up in the dialysis center. He/she will be an experienced physiotherapist and/or qualified exercise specialist who will be active in the dialysis centers for a specified number of hours per day to counsel patients concerning their worries and answer questions concerning physical activity. The EF will be properly trained by the members of the Rehabilitation Medicine Unit at the University Hospital of Ferrara on the management of frail patients by having experience with severely disabled patients with different conditions before the beginning of the study.

Stakeholder involvement: The EF, in collaboration with the team members, will prepare the informative material for the project. Team members will arrange meetings with unit personnel and coordinators of patient groups to introduce the EF figure, to explain the aims of the project and to address doubts and questions.

After the baseline outcome assessment, the EF will propose one of the four interventions to the patients by means of a specifically designed brochure, which is explained in the following section.

Qualitative outcomes will be employed in the first phase (Table 1). The rate of patients providing consent compared to the number of eligible patients, as well as the rate of patients choosing each of the training options proposed, will be calculated to determine patients’ willingness to exercise and their preferences about training. The impact of the patients’ characteristics and other variables on the choice of the program will also be investigated.

### 3.2. Phase 2

The EF will ask each enrolled patient to select an intervention and thus enter into one of the following arms.

Unstructured physical activity (U-PA)

According to each patient’s baseline physical activity level previously measured, the EF will advise patients to start or increase their spontaneous activity by counseling them on total exercise time, mode, intensity and frequency as suggested by the guidelines [27,28] (Table 2). A log-book and a wearable physical activity monitor will be provided to each patient. The instruments have to be returned in the subsequent controls, to encourage adherence and objectively measure the exercise activities.

Structured home-based low-intensity exercise (S-HB-LI)

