According to each patient’s baseline physical activity level, a semipersonalized walking program will be provided. This program, derived from previous experience with ESKD patients [13,29] was also successfully tested in other fragile populations such as stroke survivors or multiple sclerosis patients [30,31,32]. The training program will be performed at home at a prescribed speed and it includes a 10-min session/day of intermittent walking (1- or 2-min work and 1-min seated rest). The speed which is converted into a walking cadence is increased weekly and it is controlled at home with the aid of a metronome (Table 2). Patients will be provided with a daily log containing the detailed exercise prescription and free lines to provide feedback on training execution and any possible related symptoms.

Structured supervised low-intensity exercise (S-SU-LI)

Patients will meet at a specified location (room or corridor) into the dialysis unit for the exercise program in groups of a maximum of four subjects. The thirty-minute training session will be scheduled on a 2- or 3-time/week pattern, and they will be performed immediately before or after the dialysis treatment or according to patients’ preferences and considering the postdialysis fatigue that affects this population [33].

Each session will include low-intensity walking exercises (similar to those for the structured home-based training) and resistance and power exercises with elastic bands and ankle/wrist weights. Each session will begin and end with a warm-up and cool-down period of stretching, respectively. The total duration of the session will be approximately 30 min. The training intensity will be set according to the patient’s baseline capacity and it will be weekly increase. The rate of perceived exertion will be always collected (Table 2).

Physical performance assessment only (PPA)

Patients choosing this option will not begin any exercise program, but they will perform the outcome measures session only. A switch to another treatment, periodically proposed by the EF, will be always possible.

Study design is presented in Figure 1.

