### 3.6. Phase 2 Outcomes

First, the feasibility and safety of the exercise programs will be assessed in terms of adverse events, falls and intercurrent problems. In addition, the adherence of each patient to the selected training option will be determined by analyzing the number of sessions completed, the total minutes of training and the percentage of patients that reached the amount of physical activity indicated by the guidelines.

Quantitative outcomes will be collected before the beginning of the training program, at the end of the training program (three months) and at the six-month follow-up.

The primary outcome will be exercise capacity, assessed through the 6-min walking test. Subjects will be instructed to walk with their habitual walking device as far as possible in 6 min. The test will be performed on a 22-m walkway. The patients will have the possibility of slow down and rest if necessary. The total distance walked, the pain-free walking distance and the perceived exertion at the end of the test (Borg Scale 1–10) will be recorded [34] (Table 1).

Secondary outcomes will include the following:Gait speed, assessed through the 10-m walking test.Lower limb strength, evaluated with the 5-time sit-to-stand test.Health-related QoL, measured by the Italian version of the Short Form Health Survey (SF-36).Fear of falling, assessed through the Short Falls Efficacy Scale.Estimated functional capacity, measured by the Duke Activity Status Index.Depression, evaluated by the Beck Depression Inventory—II and the demoralization scale.Heart rate, oxygen saturation and blood pressureLaboratory outcomes: Serum creatinine levels, estimated glomerular filtration rate, Kt/v, glycaemia, total cholesterol and a full blood count will also be determined.Long-term outcomes: Other clinical outcomes, such as mortality and all-cause hospitalization, will be recorded at 3, 6, 12 and 24 months from the end of the exercise program.

A detailed description of secondary outcomes is available in the Supplementary Material 1.

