### 4.2. Trial Limitations

This trial presents several limitations, as it is a single-center nonrandomized study. Moreover, a typical during-dialysis treatment training option is not scheduled, despite the evidence in the literature [14,15]. However, we aim to test training solutions requiring minimal space and equipment that are implementable in most dialysis centers worldwide and not overtaxing of the personnel and the routine of a dialysis center. In addition, the study design will likely introduce a selection bias in the enrolled population, as conceivably fitter patients may opt for the walking or mixed training programs, while less fit patients may choose for the unstructured increase in physical activity; proper methods of analysis will be used to overcome the lack of randomization. These factors may limit the generalizability of the findings as well the possibly small sample size that will occur in case of limited participation of patients.

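### The only tests named for individual programmes are within-arm paired tests; statements about the most effective pathway should rest on adjusted between-arm differences

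*Protocol article*

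**What the plan says.** Section 1 of the protocol article states that "the preferred and most effective exercise pathways for the patients will be identified". It then describes the functional and clinical analyses as secondary: "the study aims to carry out exploratory analyses to evaluate the impact of different exercise interventions".

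The arms are chosen by the patients (section 3.2): "The EF will ask each enrolled patient to select an intervention and thus enter into one of the following arms". There are four: unstructured activity, structured home-based exercise, structured supervised exercise, and performance assessment only (PPA). Of PPA the article says: "Patients choosing this option will not begin any exercise program". These patients attend the outcome sessions and may switch into a programme, which the exercise facilitator will propose to them from time to time.

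Section 3.6 fixes the Phase 2 endpoint: "The primary outcome will be exercise capacity, assessed through the 6-min walking test". It is measured at baseline, 3 months and 6 months.

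For these repeated outcomes, section 3.10 names three tools, in this order:

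1. A two-way repeated-measures ANOVA for the primary and secondary outcomes.
2. Paired tests: "Within-group comparisons will be performed via paired Student’s t-tests or Wilcoxon tests, as appropriate".
3. A secondary, adjusted multivariate analysis, with a linear mixed model as the example, used if baseline characteristics are found to differ significantly between groups.

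The significance level is 0.05. Section 3.8 says that the number of patients per option cannot be known in advance. Section 4.2 accepts that "the study design will likely introduce a selection bias in the enrolled population", and expects fitter and less fit patients to choose different programmes.

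**The concern.** To say which pathway is most effective, one needs a result for each programme relative to something else. The ANOVA, read naturally as arm by time, tests whether change differs anywhere among four arms; by itself it does not say which programme differs from which. The adjusted model could say so, but it runs only after a significant baseline difference. That leaves the paired test as the only named procedure that always runs and speaks about one programme.

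A paired test cannot carry that conclusion. Change within an arm combines any programme effect with familiarity with a repeated walk test, regression to the mean and the natural course of the disease. Patients chose their arms, partly according to fitness, so these components may differ between arms. The power of each paired test also grows with the number of patients who picked that arm, so the most popular option is the likeliest to show a significant improvement, whether or not it works better.

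At stake is the Phase 2 message about which programme to offer. A pattern of significant and non-significant arms is easily reported as a ranking of programmes, although it may reflect only arm size and chance.

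**Working it through.** **Inputs from the article.** Four self-chosen arms (section 3.2); alpha 0.05, taken as two-sided because the article does not say (section 3.10); unknown arm sizes (section 3.8). Section 3.8 explains that no power calculation between programmes was possible, so there is no figure of the plan's own to reproduce on this point. Its 88 patients belong to the Phase 1 estimate of the responder rate. I borrow 88 only as a total, to make arm sizes concrete: 88 / 4 = 22.

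**Assumptions.** The article gives no effect, SD or arm sizes. All figures below are illustrations over a range.

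**Step 1: identical true change, equal power p in four independent arms.**
P(some but not all arms significant) = 1 − p⁴ − (1 − p)⁴
- p = 0.5: 1 − 0.0625 − 0.0625 = 0.875
- p = 0.8: 1 − 0.4096 − 0.0016 = 0.589
- p = 0.05 (no change in any arm): 1 − 0.05⁴ − 0.95⁴ = 0.185

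**Step 2: the same question without assuming equal power.** Simulation of 10,000 trials per cell: normal change scores, the same true change d (in SDs of change) in every arm, one follow-up time, no dropout. The F test compares mean change across arms, which is the arm-by-time test with two time points.

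| d | Mixed significance, arms 22/22/22/22 | Mixed significance, arms 35/25/18/10 | F test rejects (equal / unequal arms) |
|---|---|---|---|
| 0 | 18.8% | 18.5% | 5.0% / 4.7% |
| 0.2 | 47.9% | 47.2% | 4.7% / 5.0% |
| 0.3 | 71.6% | 72.2% | 5.0% / 5.1% |
| 0.5 | 84.2% | 89.9% | 5.0% / 4.5% |
| 0.8 | 20.3% | 46.9% | 5.1% / 4.8% |

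The between-arm test stays near its nominal 5% throughout, while paired tests disagree in up to 90% of trials.

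**Step 3: the role of arm size.** With d = 0.5 in every arm and sizes 35, 25, 18 and 10, the paired test is significant in 82%, 67%, 52% and 29% of trials. Check against step 2: 0.82 × 0.67 × 0.52 × 0.29 = 0.083 (all significant) and 0.18 × 0.33 × 0.48 × 0.71 = 0.020 (none), so mixed = 1 − 0.083 − 0.020 = 0.897, close to the simulated 0.899.

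**Step 4: what a direct contrast can deliver.** Normal approximation, 22 against 22, two-sided 0.05:
- Power is 17%, 38% and 76% for true differences of 0.3, 0.5 and 0.8 SD.
- 80% power needs 175, 63 and 25 patients per arm.
- The half-width of a 95% interval is 1.96 × √(2/22) = 0.59 SD.

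The between-arm comparison is therefore valid in form but imprecise at these sizes, and the report should show that imprecision.

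**The case against.** The strongest reply is that the plan does contrast arms. The ANOVA stands in the sentence just before the paired tests, the adjusted model in the sentence just after, and section 3.8 speaks of comparing outcomes between programmes. Section 4.2 expects baseline differences, so the adjusted model may well be triggered. All of this stands. A reader might infer that the plan replaces between-arm comparison by within-arm testing, or that the best pathway will be the arm that reaches p < 0.05. The documents support neither: no selection rule is stated, and the paired tests are not called the follow-up to the ANOVA.

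A second reply is that post hoc contrasts and a reference arm are details a condensed article may leave to a fuller plan. That also stands, and their absence alone would be no finding. What the article does fix is within-arm testing at 0.05 as the only result tied to one programme, and adjustment that depends on a baseline significance test. Those choices can be judged as written.

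Third, PPA is not a clean control. A reader might treat its change as the non-programme change of the other arms. The article does not support this: PPA is self-selected, fitness is expected to vary with choice, and its patients may switch into training. Nor does the article exclude PPA from the ANOVA.

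Fourth, the percentages depend on the assumed power: mixed significance falls to about 19% with no change and to 20% to 47% at 0.8 SD. They matter only if conclusions are read from the paired tests. Both points are correct.

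Finally, within-arm change is ordinary descriptive reporting in a nonrandomised feasibility trial, and section 1 calls these analyses exploratory. That argues for keeping the within-arm results as description and limits the weight of the point.

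**Conclusion.** The point holds in limited form. The article sets an aim that needs programme-specific conclusions. What it names for this is an omnibus ANOVA, a conditional adjusted model, and paired tests that cannot support such conclusions in self-chosen arms of unknown size. The risk is conditional: if programme-level statements were drawn from the paired tests, arms with identical true change would often look different. Under equal assumed power this happens in 87.5% of trials at 50% power per arm and in 59% at 80%. In the simulations it ranges from about 19% to 90%, depending on the common change and the split of 88 assumed patients.

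These figures rest on independent arms, normal changes, a two-sided 0.05 level and no dropout. They leave out confounding by choice, which could add real differences in change unrelated to the programmes. The trial's feasibility aims are unaffected; the interpretation of the walk test and the secondary outcomes by programme is what needs tightening.

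**What to change.** Amend section 3.10 in three respects.

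1. Make the within-arm results descriptive: mean change in each arm with a 95% interval at 3 and 6 months, and no claim of significance.
2. Base any programme-specific statement on baseline-adjusted differences between arms, with 95% intervals at 3 and 6 months, covering each programme against PPA and programme against programme. With four arms this is 3 + 3 = 6 differences per time point. Take them from the mixed model already foreseen, and fit that model whatever the baseline significance tests show; in small arms a non-significant baseline test is weak evidence of balance.
3. Label these differences exploratory, in line with section 1. State that PPA is self-selected and open to switching, so that adjustment reduces confounding but does not remove it.

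The cost is a change of wording. No new data are needed, since baseline values are already collected. The downside is fewer p values and wide intervals: about ±0.59 SD for 22 against 22, and 1.96 × √(1/35 + 1/10) = 0.70 SD for 35 against 10. The article may then have to say that no programme can be singled out.

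### Patients choose their own arm, partly by fitness, yet the main between-program comparison names no covariates, and adjustment is a secondary step triggered by a significant baseline test

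*Protocol article*

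**What the plan says.** Arms are formed by patient choice (Section 3.2, Phase 2): "The EF will ask each enrolled patient to select an intervention and thus enter into one of the following arms". Section 4.2 (Trial Limitations) predicts the direction of selection: "fitter patients may opt for the walking or mixed training programs, while less fit patients may choose for the unstructured increase in physical activity". It then promises that "proper methods of analysis will be used to overcome the lack of randomization", without naming a method there.

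The outcome in question is fixed in Section 3.6: "The primary outcome will be exercise capacity, assessed through the 6-min walking test". It is measured at baseline, three months and six months.

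Section 3.10 (Statistical Analysis) sets the order of analyses. The between-group comparison comes first: "A two-way repeated measure analysis of variance will be used to compare differences in the primary and secondary outcomes". No covariates are named. Adjustment follows under a condition: "If a significantly different distribution between the baseline characteristics of the group is identified, a secondary analysis that employs multivariate modeling to adjust", and then only for the factors found to differ. Linear mixed models are given as an example of that conditional analysis. The criterion throughout is that a p "value of 0.05 will be considered statistically significant".

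**The concern.** In a self-selected design, confounding is expected whatever a baseline test says. Letting significance decide on adjustment has three weaknesses.

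- In small arms, a non-significant test is weak evidence of comparability.
- A confounder that misses 0.05 stays out of the model even when another variable triggers adjustment.
- When the trigger fires, the adjusted result is still labelled secondary and the ANOVA remains the leading result.

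Fitness could plausibly affect change in walking distance, because Table 2 sets the content of each program by baseline six-minute distance (three bands). A difference in 6MWT change that reflects who chose a program could therefore be reported as an effect of that program. The Introduction says the study will identify which pathways work best, so such a reading is likely.

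**Working it through.** The plan gives no figure to reproduce here. Its one computed sample size, 88, concerns the precision of a response rate in phase 1. The check asks how the stated rule behaves when no program has any effect.

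**Inputs from the protocol.** Four arms; significance level 0.05 (Section 3.10); about 140 patients and 50% acceptance (Section 3.8), so 140 × 0.5 = 70 participants.

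**Assumptions not in the protocol.** Arms of 17, 18, 17 and 18. Two arms are fitter and two less fit, with a true gap of *d* = 0.5 or 0.7 SD in one measured fitness variable. Fitness correlates *ρ* = 0.2, 0.4 or 0.6 with change in 6MWT within arms. The baseline test is a one-way ANOVA. The group-by-time comparison is represented by a one-way ANOVA on change from baseline, which is exact for two visits and a simplification for three.

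**Step 1: how often the trigger fails.** The noncentrality of the baseline F-test (3 and 66 df) is λ = N(d/2)².
- d = 0.5: λ = 70 × 0.0625 = 4.375; probability of a non-significant test 63%.
- d = 0.7: λ = 70 × 0.1225 = 8.575; probability 34%.

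With 88 patients (22 per arm) and d = 0.5, λ = 88 × 0.0625 = 5.5. The four-group test then misses the gap 54% of the time, and a two-arm t-test misses it 63% of the time.

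**Step 2: false positives without adjustment.** With within-arm SD of change equal to 1, arm means of change differ by ρd although no program works, so λ = N(ρd/2)². For d = 0.5 and ρ = 0.6, λ = 70 × 0.15² = 1.575.

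**Step 3: other ways of reading the results.** The last three columns are simulated, 8,000 trials per setting.

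| d | ρ | λ | Unadjusted, all trials | Unadjusted, untriggered trials only | Adjusted result replaces it when triggered | Always adjusted |
|---|---|---|---|---|---|---|
| 0.5 | 0.2 | 0.175 | 6.0% | 4.8% | 5.0% | 4.8% |
| 0.5 | 0.4 | 0.700 | 9.2% | 6.6% | 5.9% | 4.9% |
| 0.5 | 0.6 | 1.575 | 15.2% | 7.4% | 6.6% | 5.1% |
| 0.7 | 0.2 | 0.343 | 7.0% | 6.4% | 5.8% | 5.6% |
| 0.7 | 0.4 | 1.372 | 13.7% | 7.5% | 6.1% | 5.3% |
| 0.7 | 0.6 | 3.087 | 26.7% | 8.5% | 6.4% | 4.9% |

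The untriggered column is the least precise. Repeated runs put it at up to about 10% in the last row.

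**Step 4: where the false positives arise.** At d = 0.7 and ρ = 0.6, untriggered trials contribute 0.34 × 8.5% = 2.9 points of the 26.7%. At d = 0.5 and ρ = 0.6 they contribute 0.63 × 7.4% = 4.7 points of the 15.2%. The rest comes from trials in which the imbalance is detected and the plan would run an adjusted model, but as a secondary analysis.

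**Step 5: bias in the estimate.** The expected spurious difference in change is ρd. For example, 0.5 × 0.5 = 0.25 SD. In simulated two-arm comparisons (22 per arm, ρ = 0.3 or 0.5, d = 0.3 to 0.8), the average bias left in untriggered trials was 0.07 to 0.22 SD.

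**The case against.** Several points on the other side are sound.

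- A reader might infer that the comparison carries the whole of the selection bias. It does not. The group-by-time term removes a constant baseline gap in the outcome, and only factors that predict change still bias the contrast.
- A reader might also infer that undetected imbalance is the main danger. Step 4 shows otherwise: error within untriggered trials is about 5–10%, and the larger rates depend on the unadjusted result being read when an adjusted one exists.
- It is tempting to add that a repeated-measures ANOVA loses patients with a missed visit. Section 3.10 plans multiple imputation, so this carries no weight.
- The correlations have no source in the protocol, and at 0.2 the inflation is small. Section 4.2 says nothing about the fitness of the assessment-only arm, so the split into two fitter and two less fit arms is a modelling choice.
- Several fitness measures are taken at baseline, so the chance that at least one triggers adjustment exceeds the single-variable figure.
- The 5% under constant adjustment holds by construction, with one confounder, measured without error and correctly modelled. Real choice may also depend on motivation and comorbidity.
- This is a feasibility trial that calls its intervention comparisons exploratory, claims no power for them and discloses the selection bias. A detailed covariate list may sit in an analysis plan not shown, so its absence is not a fault.

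These points limit the size and severity. They do not remove the fault, because the order of analyses is stated in the protocol. 6MWT is the named primary outcome, and best-performing pathways are to be identified at the 0.05 level.

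**Conclusion.** The point holds in a limited form and should be fixed; it does not invalidate the trial. In a design where selection by fitness is foreseen, Section 3.10 gives the leading place to a comparison with no covariates named. Adjustment is left secondary and dependent on a significance test. Under the assumptions above, the leading analysis has a false-positive rate of about 6–7% for a weak link between fitness and change. For moderate to strong links the rate is about 9–15% (0.5 SD gap) or 14–27% (0.7 SD gap). Most of that excess comes from the secondary status of the adjusted model. The trigger adds a smaller error and leaves biased estimates when it does not fire. The documents do not support saying that the comparison is wholly confounded, or that adjustment would turn the contrasts into program effects.

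**What to change.** In Section 3.10, make the linear mixed model already named there the main between-program analysis of 6MWT and the secondary outcomes. Adjust it always for a short pre-specified set of baseline variables the study already collects or plans to use: baseline value of the outcome, age, sex and baseline daily steps. Add the choice-related factors that Section 3.10 names for phase 1 (caregiver, distance from the center) as numbers allow. Remove the significance trigger. Keep the ANOVA as a sensitivity analysis. State that between-program contrasts will be reported as associations, because unmeasured confounding remains.

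The cost is a change of wording, a few degrees of freedom, and reliance on the adjustment model, including the assumptions involved in adjusting for a baseline outcome value in groups that were not randomized. No new data are needed.
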